# ISOlation Procedure vs. conventional procedure during Distal Pancreatectomy (ISOP-DP trial): study protocol for a randomized controlled trial

**DOI:** 10.1186/s13063-021-05523-y

**Published:** 2021-09-16

**Keywords:** Distal pancreatectomy, Distal pancreatosplenectomy, Isolation, Radical antegrade modular pancreatosplenectomy

## Abstract

**Background:**

Radical antegrade modular pancreatosplenectomy (RAMPS) is an isolation procedure in pancreatosplenectomy for pancreatic body/tail cancer. Connective tissues around the bifurcation of the celiac axis are dissected, followed by median-to-left retroperitoneal dissection. This procedure has the potential to isolate blood and lymphatic flow to the area of the pancreatic body/tail and the spleen to be excised. This is achieved by division of the inflow artery, transection of the pancreas, and then division of the outflow vein in the early phases of surgery. In cases of pancreatic ductal adenocarcinoma (PDAC), the procedure has been shown to decrease intraoperative blood loss and increase R0 resection rate by complete clearance of the lymph nodes. This trial investigates whether the isolation procedure can prolong the survival of patients with pancreatic ductal adenocarcinoma who undergo distal pancreatosplenectomy (DPS) compared with those that undergo the conventional approach.

**Methods/design:**

Patients with PDAC scheduled to undergo DPS are randomized before surgery to undergo either a conventional procedure (arm A) or to undergo the isolation procedure (arm B). In arm A, the pancreatic body, tail, and spleen are mobilized, followed by removal of the regional lymph nodes. The splenic vein is transected at the end of the procedure. The timing of division of the splenic artery (SA) is not restricted. In arm B, regional lymph nodes are dissected, then we transect the root of the SA, the pancreas, then the splenic vein. At the end of the procedure, the pancreatic body/tail and spleen are mobilized and removed. In total, 100 patients from multiple Japanese high-volume centers will be randomized. The primary endpoint is 2-year recurrence-free survival by intention-to-treat analysis. Secondary endpoints include intraoperative blood loss, R0 resection rate, and overall survival.

**Discussion:**

If this trial shows that the isolation procedures can improve survival with a similar R0 rate and with a similar number of lymph node dissections to the conventional procedure, the isolation procedure is expected to become a standard procedure during DPS for PDAC. Conversely, if there were no significant differences in endpoints between the groups, it would demonstrate justification of either procedure from surgical and oncological points of view.

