### Statistical analysis

#### Sample size

Clinical trials of isolation and conventional procedures during distal pancreatectomy for pancreatic body/tail cancer have not been widely reported. A two parallel multicenter randomized selection phase II trial compared the conventional procedure with isolation procedure as a basis for a future phase III trial [18]. Its principal aim was to evaluate whether the isolation procedure has a better 2-year recurrence-free survival rate than the conventional procedure in DPS for PDAC. In an observational study, Abe et al. reported that the recurrence rate during the approximately 2-year follow-up period of the conventional procedure was 75%, whereas that of the isolation procedure was 67% [7]. In the current study, we also assume that each group will have a similar 2-year progression-free survival rate. We therefore calculated the number of patients required on the basis of a selection design so that the conventional procedure arm would select a regimen with a 2-year recurrence-free survival rate 8% higher than the expected value with 80% probability. The minimum required number of cases is 46 cases per group. Assuming that approximately 10% of ineligible cases will occur, the target number of registered cases is set to 50 per group (100 cases in total).

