#### Statistical analysis plan

The primary population for efficacy analysis will be the intention-to-treat population, defined as all randomized patients. The primary endpoint is the 2-year RFS rate. The primary analysis will be based on the full analysis set (FAS), which consists of all randomized patients except those found to be ineligible after enrollment. The Kaplan-Meier method will be used to estimate the progression-free survival curve and 2-year progression-free survival rate. The regimen with a higher 2-year progression-free survival rate will be considered as the more promising procedure of the two. The Brookmeyer-Crowley method will be used to calculate the 95% confidence interval for the 2-year progression-free survival rate. Although the design of choice cannot confirm the results based on a hypothetical test, it would compare the progression-free survival curves using the log-rank test as a reference. A Cox proportional hazard model will be applied to calculate HRs and 95% confidence intervals adjusted for stratification factors (i.e., approach method and preoperative adjuvant therapy). For evaluation of secondary endpoints, categorical outcomes will be summarized using frequency and percentage for each arm and will be compared using Fisher’s exact test. Mann-Whitney-Wilcoxon test will be used to compare continuous outcomes and will be summarized using the median and interquartile range.

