In an international multicenter study, Korrel et al. reported that Gerota’s fascia resection, R0 resection, and reduction in LNR were factors associated with improved overall survival in DP-treated PDAC [24, 25], but the surgical approach was not included as a risk factor in their analysis. There is a possibility that the squeezing out of tumor cells can be reduced by a surgical approach. It has become possible in recent years to observe and manipulate the deep abdominal cavity and the retroperitoneal space in detail with a laparoscopic field of view and developed surgical devices. As a result, the oncological impact of the isolation technique may be greater than the difference in the direction of the retroperitoneal dissection. If there is an oncological benefit in the RAMPS procedure, it may be due to early blockage of the lymphatic, arterial, and portal venous system in the pancreatic body/tail by prioritizing the vascular dissection in the excision phase. However, the oncological benefits of this surgical procedure have not yet been demonstrated in prospective randomized controlled trials.

If the ISOP-DP trial shows that the isolation procedure can improve recurrence-free survival with a similar R0 rate and a similar number of lymph node dissections to the conventional procedure, the isolation procedure is expected to become a worldwide standard procedure during DPS for PDAC under the concept of isolation technique. Otherwise, if there are no significant differences in endpoints between the groups, it will demonstrate that both procedures may be justified from surgical and oncological points of view.

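### The Discussion says that no significant differences would demonstrate that either procedure is justified; the selection design cannot support that, and the Statistical analysis plan section says as much

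*Protocol article*

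**What the plan says.** - **Abstract, Discussion:** "if there were no significant differences in endpoints between the groups, it would demonstrate justification of either procedure", with surgical and oncological viewpoints both named.
- **Main Discussion, last paragraph:** "if there are no significant differences in endpoints between the groups, it will demonstrate that both procedures may be justified", again on surgical and oncological grounds. This is softer because of the words may be, but it keeps the verb demonstrate.
- **Statistical analysis plan:** the arm with the higher 2-year rate is taken as the more promising. "Although the design of choice cannot confirm the results based on a hypothetical test", the survival curves are compared by log-rank test for reference only. Hazard ratios with 95% confidence intervals, adjusted for stratification factors, are planned.
- **Sample size:** the trial is a randomised selection phase II meant to inform a later phase III. The planning values come from an observational study with recurrence of 75% (conventional) and 67% (isolation) over about 2 years. The aim is to select an arm with a "2-year recurrence-free survival rate 8% higher than the expected value with 80% probability". This leads to at least 46 patients in each arm, raised to 50 to allow for ineligible cases.
- **Study design and overview:** the aim is framed as superiority of the isolation procedure. No equivalence or non-inferiority margin appears anywhere in the article.

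**The concern.** The two Discussion sentences attach a positive conclusion to the absence of significance. To show that either procedure is acceptable on oncological grounds, a trial must exclude a difference that matters. That takes a margin and enough information to rule the margin out, and the article provides neither. The 80% in the Sample size section is a probability of picking the better arm. It is not the power of a test.

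The Discussion and the statistical section also give different readings of the same data. Suppose the isolation arm has the higher 2-year RFS with a log-rank p-value above 0.05. The Statistical analysis plan section then names isolation as the more promising procedure, while the Discussion says the trial has demonstrated that either is justified. As the working shows, non-significance is the most likely outcome at the planned effect. The headline conclusion in the commonest case would therefore be one the trial cannot support: a sizeable benefit or harm in recurrence would remain compatible with the data.

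**Working it through.** **Inputs.** Recurrence of 75% and 67% at about 2 years, 46 and 50 per arm (Sample size); 1:1 allocation (Randomization); 2 years of recruitment plus 2 years of follow-up (Study design and overview). Recurrence is taken as the complement of RFS, giving 25% and 33%. Assumptions not stated in the article: proportional hazards and the test level. Two-sided 5% is used to match the planned 95% intervals, with one-sided 5% shown as the range.

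**1. The plan's own figure.** For a pick-the-winner design, n = z(0.80)² × [p1(1−p1) + p2(1−p2)] / (p2−p1)² = 0.8416² × (0.1875 + 0.2211) / 0.08² = 45.2, so 46 per arm. An exact binomial calculation with ties split evenly gives a correct-selection probability of 0.801 at 46, the first n to reach 0.80. The stated size reproduces.

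**2. Hazard ratio and events.** HR = ln(0.33)/ln(0.25) = 0.80, so |ln HR| = 0.2235. Events by 2 years: 50 × 0.75 + 50 × 0.67 = 71; with 46 per arm, 65.3.

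**3. Log-rank power.** Power = Φ(√events / 2 × |ln HR| − z).

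| Events counted | Two-sided 5% | One-sided 5% |
|---|---|---|
| To 2 years, 46 per arm (65.3 events) | 14.5% | 22.9% |
| To 2 years, 50 per arm (71 events) | 15.4% | 24.1% |
| All follow-up to year 4, 46 per arm (76.6 events) | 16.3% | 25% |
| All follow-up to year 4, 50 per arm (83.3 events) | 17.4% | 27% |

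For example, with 71 events: √71 / 2 × 0.2235 − 1.96 = −1.018, and Φ(−1.018) = 0.154. The year-4 rows assume uniform accrual and exponential times. Their one-sided entries come from the same formula; with 83.3 events, 1.020 − 1.645 = −0.625 and Φ(−0.625) = 0.27. A simulation of 20,000 trials censored at 2 years gave 14.5% (46 per arm) and 16.4% (50 per arm), two-sided.

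**4. Chance of a non-significant result if the planned benefit is real.** With events to 2 years: 1 − 0.145 = 85% down to 1 − 0.241 = 76%. The most favourable cell of the table (one-sided, all follow-up) would lower this to 73%. By symmetry, a harm of the same size on the log hazard scale would go undetected about as often by a two-sided test.

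**5. Precision.** The half-width for the difference in 2-year RFS is 1.96 × √[(0.1875 + 0.2211)/n] = 17.7 points (n = 50) or 18.5 points (n = 46). If both arms were observed at 25%, it is 1.96 × √(2 × 0.1875/n) = 17.0 or 17.7 points. If the observed HR were exactly 1 with 71 events, the interval is exp(±1.96 × 2/√71) = 0.63 to 1.59. Neither interval excludes the planned 8 points or HR 0.80.

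**6. For scale.** A two-sided 5% log-rank test with 80% power would need 4 × (1.96 + 0.8416)² / 0.2235² = 629 events.

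**The case against.** Both sentences are forward-looking Discussion prose and not the analysis rule. The operative rule is the selection rule in the Statistical analysis plan section, which does not treat non-significance as evidence of anything and already provides hazard ratios with confidence intervals. This stands: the fault lies in the pre-stated interpretation, and the planned analysis is not shown to be wrong.

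The wording can also be read mildly. The article notes under Standardization and validation of interventions that both procedures are in daily use, so without evidence favouring one, using either remains defensible. A reader might infer that the authors mean to declare the procedures equivalent or interchangeable, but neither word appears. The milder reading is available, but it sits badly with a claim to demonstrate justification on oncological grounds, so it softens the point without removing it.

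A reader might also infer that a non-significant result could wrongly halt the later phase III trial. The documents do not support that: nothing ties a phase III decision to significance, and the selection rule picks an arm whatever the p-value.

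Nor does low log-rank power mean the trial is too small. The 46 per arm is right for its stated purpose.

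Lastly, the power figures depend on a test level the article does not give, and they cover RFS only, whereas the sentences speak of endpoints in general. Both limits stand. Across the levels shown, non-significance remains the expected result.

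**Conclusion.** The point holds as a conflict between the Discussion statements and the design. The article says a non-significant result would demonstrate justification of either or both procedures; it sets no margin, and its own statistical section disclaims confirmation by test. At the planned effect, RFS log-rank power is about 15 to 17% (two-sided 5%) or about 23 to 24% (one-sided 5%, events to 2 years). Non-significance is then expected in roughly 76 to 85% of trials with a real 8-point benefit, and the interval for the difference is about ±17 to 18 points, around twice the planned effect. This rests on proportional hazards, on recurrence as the complement of RFS, and on an assumed test level; the direction does not depend on which level is chosen. The sample size and the selection rule are not challenged.

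**What to change.** Delete both sentences, or reword them to say that the trial is not designed to show equivalence, that a non-significant result is inconclusive, and that it will not be read as similarity. Report the between-arm difference in 2-year RFS with its 95% confidence interval, next to the hazard ratio and interval already planned. Limit the conclusion to which procedure is the more promising under the selection rule in the Statistical analysis plan section.

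The cost is text and one added interval. Sample size, randomisation, conduct and primary analysis are unchanged. The downside is that the conclusion open to the authors after a non-significant result becomes less favourable.

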**Trial registration:**

UMIN Clinical Trials Registry UMIN000041381. Registered on 10 August 2020. ClinicalTrials.gov NCT04600063. Registered on 22 October 2020.

**Supplementary Information:**

The online version contains supplementary material available at 10.1186/s13063-021-05523-y.

## Background

Several investigators have advocated the possibility that grasping tumors during pancreatectomy may increase the risk of squeezing and thus shedding cancer cells into the portal vein, retroperitoneum, and/or peritoneal cavity [1, 2]. To overcome these problems, a number of surgical techniques have been proposed, aiming for non-touch pancreatectomy [3].

Many gastroenterological surgeons have tried to demonstrate oncological benefits of such non-touch techniques, similar in concept to the isolation technique for resection of several gastrointestinal cancers. The impact of the isolation technique has not yet been demonstrated by scientifically acceptable methods [3, 4]. Considering the portal venous system as a drainage vein of the pancreatic body/tail and spleen, we suggest the anatomical features may be suitable for verification of the oncological benefits of the isolation technique.

Radical antegrade modular pancreatosplenectomy (RAMPS) was reported by Strasberg et al. in 2003 as a new antegrade procedure which provides improved visibility and allows removal of N1 nodes. It permits adjustment of the depth of the posterior extent of resection coupled with early rather than late control of the vasculature. Descriptions of the RAMPS procedure indicate the potential of isolation of blood and lymphatic flow to the area of the pancreatic body/tail and spleen to be excised [5, 6]. This is achieved by dividing the inflow artery, transecting the pancreas, and dividing the outflow vein in the early phases of surgery.

The RAMPS method has since been reported to have oncological usefulness as a favorable method for each lymph node dissection and R0 resection in multiple institutions [7–12], but all of these studies have been retrospective historically controlled studies. RAMPS performed in recent years, with the development of surgical techniques and devices, has been compared with the conventionally used procedures. No randomized controlled studies have yet compared the clinical usefulness of the isolation procedure with the conventional procedures as a control group in distal pancreatosplenectomy (DPS) for patients with pancreatic ductal adenocarcinoma (PDAC).

To confirm the results of the cohort study, we will conduct a multicenter, randomized, placebo-controlled phase II trial of the isolation procedure (ISOP-DP trial). We will evaluate whether it affects the recurrence-free survival (RFS) rate compared with conventional procedures after DPS. This trial is registered at the UMIN Clinical Trials Registry (UMIN000041381) and at ClinicalTrials.gov (NCT04600063).

## Methods/design

### Study design and overview

The ISOP-DP trial is a Japanese multicenter, randomized, controlled trial. Patients with PDAC are randomized to arm A (conventional procedure) or arm B (isolation procedure) during DPS. The ISOP-DP trial is conducted in 11 Japanese high-volume centers (Additional file 1, institution list) that have been board-certified as training institutions by the Japanese Society of Hepato-Biliary-Pancreatic Surgery. To ensure the high quality of the study, interventions are performed by instructors and expert surgeons certified by the society. This study aims to evaluate the oncological and surgical benefits of the isolation procedure during DPS for patients with PDAC in comparison with the conventional procedure. This study is therefore designed to evaluate the superiority of the isolation procedure (arm B) compared with the conventional procedure (arm A) during DPS in terms of a 2-year recurrence-free survival (RFS) rate. All patients are required to undergo postoperative examination every 3 months for at least 2 years after surgery. Signs of suspected disease recurrence will be closely monitored. The schedule of this trial is shown in Fig. 1. The study period of the ISOP-DP trial is expected to be 4 years, including 2 years for patient recruitment and 2 years of follow-up.

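### The objective and conclusions claim superiority and a new standard, but the trial is sized and decided as a pick-the-winner selection study that cannot support them or the opposite conclusion of no difference

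*Protocol article*

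**What the plan says.** All references are to the protocol article.

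- **Study design and overview.** The trial is "designed to evaluate the superiority of the isolation procedure (arm B) compared with the conventional procedure (arm A", on the 2-year RFS rate.
- **Sample size.** The design is given as follows: "A two parallel multicenter randomized selection phase II trial compared the conventional procedure with isolation procedure as a basis for a future phase III trial". The assumed 2-year recurrence rates are 75% (conventional) and 67% (isolation), taken from an observational study. The sizing criterion is that "the conventional procedure arm would select a regimen with a 2-year recurrence-free survival rate 8% higher than the expected value with 80% probability". This gives 46 per group, raised to 50 for ineligible cases.
- **Statistical analysis plan.** The decision rule is: "The regimen with a higher 2-year progression-free survival rate will be considered as the more promising procedure of the two". I take progression-free here to mean the RFS primary endpoint. The section concedes that the design cannot confirm a result by hypothesis test and keeps the log-rank test for reference. It states no alpha for the primary comparison.
- **Discussion, and the Discussion paragraph of the abstract.** If isolation improves outcome with a similar R0 rate and lymph node yield, then "the isolation procedure is expected to become a worldwide standard procedure during DPS for PDAC"; the abstract says a standard procedure, without the word worldwide. If there are no significant differences, both places say this would demonstrate that either procedure is justified.

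**The concern.** A superiority trial and a selection trial answer different questions. A superiority trial limits the chance of declaring a benefit that does not exist. A two-arm selection trial limits only the chance of picking the worse arm when the arms differ by a stated amount, and it always names a winner. The article states the first objective but builds the second design, and both of its closing conclusions need properties of the first.

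Two misreadings could follow. A numerically higher rate for isolation could be reported as having met a superiority objective. A non-significant reference test could be reported as showing that the choice of procedure does not matter. The sizing sentence makes the first more likely: it attributes the 80% to the conventional arm selecting a regimen, which describes nothing an arm can do, and a reader could take the figure for 80% power.

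**Working it through.** **Inputs.** From Sample size: 2-year RFS of 1 − 0.75 = 0.25 (conventional) and 1 − 0.67 = 0.33 (isolation), difference 0.08, target probability 80%, 46 per group minimum, 50 per group registered. My assumption, since the article gives none: two-sided alpha of 0.05 for any superiority test.

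**1. Reproducing 46 per group.** For a two-arm selection design,

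n = z(0.80)² × [p₁(1−p₁) + p₂(1−p₂)] / (p₂−p₁)²

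= 0.8416² × (0.1875 + 0.2211) / 0.0064 = 0.7083 × 0.4086 / 0.0064 = 45.2, so 46.

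The plan's figure is reproduced. By exact binomial enumeration at 46 per arm, isolation has the higher count with probability 76.9% and ties with probability 6.4%. Correct selection is 76.9 + 3.2 = 80.1% with ties split. The 80% is therefore the probability that the truly better arm shows the higher rate when the true rates are 25% and 33%.

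**2. The same rule under other true rates** (exact binomial, simple proportions):

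| True RFS, conventional / isolation | n per arm | Isolation strictly higher | Isolation selected, ties split |
|---|---|---|---|
| 25% / 25% | 46 | 45.2% | 50% |
| 25% / 25% | 50 | 45.4% | 50% |
| 25% / 21% | 50 | 27.6% | 31.8% |
| 25% / 17% | 50 | 13.3% | 16.3% |
| 33% / 25% | 46 | 16.7% | 19.9% |

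**3. Power if the data were tested for superiority at the planned effect.**

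*Proportions.* The pooled rate is 0.29. Power ≈ Φ{[0.08 − 1.96 √(2 × 0.29 × 0.71 / n)] / √(0.4086 / n)}.

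- n = 46: (0.08 − 1.96 × 0.0946) / 0.0942 = −1.12, power 13.2%.
- n = 50: (0.08 − 1.96 × 0.0908) / 0.0904 = −1.08, power 13.9%.

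*Log-rank.* Under proportional hazards, HR = ln 0.33 / ln 0.25 = 0.80 and |ln HR| = 0.2235. Power ≈ Φ(0.2235 × √events / 2 − 1.96). The average 2-year event proportion is (0.75 + 0.67) / 2 = 0.71, giving about 65 events in 92 patients and 71 in 100. I also take 80 events, to allow for follow-up beyond 2 years.

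- 65 events: 14.5%
- 71 events: 15.4%
- 80 events: 16.8%

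**4. Scale.** The expected 95% confidence interval half-width for the difference is 1.96 × 0.0942 = 18.5 points at 46 per arm and 1.96 × 0.0904 = 17.7 points at 50, against an assumed difference of 8 points. At 80% power and two-sided 0.05, a superiority comparison of 25% with 33% would need

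n = {[1.96 √(2 × 0.29 × 0.71) + 0.8416 √0.4086] / 0.08}² = 503.8, so 504 per arm.

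**The case against.** The strongest defence is that nothing is hidden. The Background calls the trial phase II, Sample size names the selection design and the later phase III trial, and the Statistical analysis plan calls the winner only more promising and disclaims confirmatory testing. This stands. The fault is inconsistency, not concealment, and the sample size is correct for the design described.

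A reader might also infer that isolation would become a standard merely by being selected, so that practice could change on a 50% chance under no effect. The documents do not support that. The Discussion and the abstract set their favourable branch against the absence of significant differences, add conditions on R0 rate and lymph node yield, and say only that isolation is expected to become a standard. The 50% belongs to the label of more promising procedure. If the favourable branch means a two-sided 5% test, the chance of a false result in isolation's favour would be about 2.5%. What remains wrong is that both conclusions lean on a test that the analysis plan reserves for reference, in a trial not sized for it.

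Finally, Standardization and validation of interventions says both procedures are already in daily use, so picking either when they are equal costs little on this endpoint. That lowers the consequence of a wrong pick. It does not reconcile the objective with the design, and the selection disclosures do not reach the abstract, which mentions neither selection nor phase III.

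**Conclusion.** The concern holds as a contradiction within the article. The objective in Study design and overview, and both conclusions in the Discussion and abstract, claim what the Sample size and Statistical analysis plan sections do not provide and partly disclaim.

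The 46 per group is right, but only as a selection size with about 80% probability of correct selection at 25% vs 33%. The rule picks isolation 50% of the time when the rates are equal (about 45% counting strict wins only). When isolation is 8 points worse, it picks it 16% (17% vs 25%, 50 per arm) to 20% (25% vs 33%, 46 per arm) of the time. Power for superiority at the planned effect is about 14% for proportions and about 15% to 17% for a log-rank test. A claim of established superiority and a claim that no difference justifies both procedures are therefore both unsupported.

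The selection figures rest on simple binomial proportions in place of Kaplan-Meier estimates. The power figures rest on an assumed two-sided alpha of 0.05 and, for the log-rank test, on proportional hazards and 65 to 80 events.

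**What to change.** Amend the text in three places:

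1. **Study design and overview.** Replace the superiority objective with selection of the more promising procedure to test in a phase III trial.
2. **Sample size.** Restate the 80% as the probability that the truly better arm shows the higher 2-year RFS rate when the true rates are 25% and 33%. Add that the probability of selecting isolation is 50% when the true rates are equal.
3. **Discussion and abstract.** Replace the expectation of a standard, or worldwide standard, procedure with progression to a confirmatory phase III trial. Replace the statement that no significant difference would justify both procedures with a statement that such a result would be inconclusive.

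Sample size, randomization, conduct and follow-up do not change. The cost is that the stated claims become less favourable. Keeping the superiority objective instead would mean stating an alpha and resizing, to about 504 per arm under the assumptions above.
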